### Sample size calculation

An analysis of 5907 unique ED visits with blood culture sampling in Amsterdam UMC showed a 30-day mortality rate of 7.6%, a hospital admission rate of 67.4% and an average length of stay in the hospital of 6.7 days. Based on these numbers, the sample sizes with a relative non-inferiority margin of 1.25 for the rates and 1 day for the length of stay were calculated. The sample sizes were calculated by a statistician based on a one-sided alpha of 5% and a target power of at least 80%. For 30-day mortality, the calculated sample size was 6066 (3033 per arm) to test non-inferiority. After inflation for a dropout rate of 20%, the final sample size is 7584 (3792 per arm). For the secondary outcomes, described in table 2, fewer participants were needed for adequate power.

**Table 2 T2:** Overview of outcome measures

Primary outcome	30-day all-cause mortality
Key secondary outcomes	In-hospital mortality
	Hospital admission rates
	Hospital length-of-stay
Other outcome measures	
Patient-related outcomes	90-day mortality
	30-day readmission rates
	Emergency department length-of-stay in hours
Diagnostics related outcomes	Percentage of blood cultures avoided in the intervention group
	Number of blood cultures on each day of hospital stay (in admitted patients)
	Percentage of positive blood cultures in each group
	Total number of laboratory and microbiology tests in the ED
	Total number of laboratory and microbiology tests on each day of hospital stay (in admitted patients)
Therapy-related outcomes	Percentage of patients receiving antibiotics in the ED
	Duration of antibiotic therapy
	Types of antibiotics given in the ED
Model-related outcomes	Model performance (AUC) during the trial
	Model performance in subgroups: Immunocompromised patients (triple immunosuppressive therapy) Patients who had transplants

AUC, area under the operating curve; ED, emergency department.

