### Statistical analysis

We will carry out a per-protocol analysis. The primary outcome, the 30-day mortality rate, will be compared between the groups using a non-inferiority test for the ratio of two proportions. This will be a one-sided test with a significance level of 0.05. Additionally, we will do a multivariable analysis of the primary and key secondary outcomes to adjust for potential effect of age, Charlson Comorbidity Index, use of immunosuppressive medication, Modified Early Warning Score and resuscitation status. Similar tests will be performed for in-hospital mortality rate and the hospital admission rate. The hospital length-of-stay will be analysed as a continuous variable and a non-inferiority test for the differences between the two means will be used. The test statistic to be used is a one-sided T-test with a significance level of 0.05. The model-related outcomes will be assessed using an area under the curve and calibration plots. Baseline characteristics will be presented using descriptive statistics, without statistical testing for differences, since this is a randomised trial.

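### Length of stay is tested as a raw difference in means with no stated denominator: a death in hospital counts as a short stay, and an analysis of admitted patients only would count spared short admissions as harm

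*Protocol article*

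**What the plan says.** Table 2 of the protocol article lists hospital length of stay as a key secondary outcome, beside in-hospital mortality and hospital admission rate. The Statistical analysis section fixes the method: "The hospital length-of-stay will be analysed as a continuous variable and a non-inferiority test for the differences between the two means will be used". It continues: "The test statistic to be used is a one-sided T-test with a significance level of 0.05". A covariate-adjusted analysis of the key secondary outcomes is planned in addition.

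The Sample size calculation section sets a "relative non-inferiority margin of 1.25 for the rates and 1 day for the length of stay". Its planning values come from 5907 earlier emergency department visits: 30-day mortality of 7.6%, and "a hospital admission rate of 67.4% and an average length of stay in the hospital of 6.7 days". The text does not say whether the 6.7 days is a mean over all visits, with zeros for patients sent home, or over admissions only. It does not say which of these groups the trial will test, and it gives no rule for patients who die in hospital. Table 2 restricts two other rows to admitted patients but puts no such restriction on length of stay.

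**The concern.** Two features of the stated test can move the result for reasons other than how long patients need hospital care.

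The first is death. It ends a stay, so it shortens the arm's mean. The trial withholds a diagnostic analysis and takes mortality as its safety question. Excess early deaths would move length of stay towards non-inferiority.

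The second is the denominator. At the planning rate of 67.4%, about a third of patients have no stay. If they are left out, the arms are compared after selection on admission, which happens after randomisation and is itself a key secondary outcome. The intervention has a route to change it: under Study design and Allocation and randomisation, unblinded physicians in the intervention arm see the prediction and control physicians do not. If the prediction spares some patients a brief admission, those remaining have longer stays on average, and a benefit reads as harm.

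What is at stake is the meaning of one key secondary non-inferiority claim. The Introduction and Discussion name prolonged stay as a harm of contaminated cultures, so readers will give this result weight.

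**Working it through.** **Inputs from the Sample size calculation section.** Mortality 7.6%; ratio margin 1.25; admission rate 67.4%; mean stay 6.7 days; length-of-stay margin 1 day; one-sided alpha 5%; power at least 80%; 3033 per arm before dropout, 3792 after.

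**Assumed, because the article does not give them.** Bed-days lost per extra death, 2 to 15; share of participants spared an admission, 5% or 10%; length of a spared admission, 2 days; standard deviation of stay, 8 to 12 days.

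**The plan's own figure.** The Farrington–Manning score test for a ratio of two proportions (0.076 in both arms, margin 1.25, one-sided 5%, 80% power) gives 3033 per arm, as stated. Then 3033/0.8 = 3791.25, rounded up to 3792 per arm, or 7584 in all. No sample size or standard deviation is given for length of stay, so that outcome has no figure to reproduce. The statement that it needs fewer participants is consistent with any standard deviation up to about 15.7 days at 3033 per arm, or 12.9 days if only the admitted count (0.674 × 3033 = 2044 per arm).

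**Deaths.** Mortality at the margin is 1.25 × 7.6% = 9.5%, which is 1.9 points more. Shift in the mean over all participants = −0.019 × bed-days lost per extra death, if every extra death falls in hospital:

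- 2 days lost: −0.019 × 2 = −0.04 day
- 15 days lost: −0.019 × 15 = −0.29 day

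That is 4% to 29% of the 1-day margin, in the intervention's favour.

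**Admitted patients only.** With admission rate a, mean among the admitted m, spared share x and spared stay s, the new mean is (a·m − x·s)/(a − x).

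If 6.7 days is the mean among the admitted:

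- x = 5%: (0.674 × 6.7 − 0.05 × 2)/(0.674 − 0.05) = 4.416/0.624 = 7.08 days, a rise of 0.38
- x = 10%: (0.674 × 6.7 − 0.10 × 2)/(0.674 − 0.10) = 4.316/0.574 = 7.52 days, a rise of 0.82

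Over all participants the change is −x·s: −0.10 and −0.20 day. Nobody stays longer in either case.

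If 6.7 days is instead the mean over all visits, the mean among the admitted is 6.7/0.674 = 9.94 days, and the same shares raise it by 0.64 and 1.38 days. The 1-day margin is 15% of 6.7 days but 10% of 9.94, so the unstated denominator also changes how strict the margin is.

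**Effect on power, admitted only.** Power = Φ[(1 − shift)/(SD·√(2/2044)) − 1.645], ignoring the small further loss of admitted patients:

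| SD (days) | no shift | shift 0.38 | shift 0.82 |
|---|---|---|---|
| 8 | 99% | 80% | 18% |
| 10 | 94% | 63% | 14% |
| 12 | 85% | 50% | 12% |

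**The case against.** The strongest reply is that the larger effect depends on an analysis the article never announces. Length of stay is not restricted to admitted patients in Table 2, although two other rows are, so reading it as covering all participants is at least as natural. With zeros for those not admitted, the selection problem disappears. A condensed article may also leave the denominator and the handling of deaths to the full protocol or analysis plan. This stands: the selection effect is conditional, and a reader who infers that the trial will analyse only admitted patients goes beyond the text.

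The spared shares have no anchor either. The model section expects about 30% of analyses to be avoidable, so sparing 5% or 10% of all participants an admission means one in six or one in three of those with a cancelled analysis. No passage supports such rates, and even the 0.82-day shift lies inside the margin as a point estimate. This also stands; the figures are illustrations.

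A reader might further infer that harm could pass as benefit. The documents do not support that for the trial as a whole. The death effect is small even at the full mortality margin, its upper end assumes a loss of more than twice the mean stay, and only deaths in hospital shorten a stay. Mortality is reported at 30 days, in hospital and at 90 days, and admission rate is tested separately, so a reader would see the deaths or the fall in admissions beside the stay result. The planning rates also come from earlier visits, and trial participants may differ.

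What the reply does not remove is that the estimator and the test are positively stated. Zeros for patients not admitted cure the selection but leave deaths counted as short stays.

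**Conclusion.** The point holds in a limited form. The stated comparison of raw means counts a death in hospital as a short stay. The resulting shift is about 0.04 to 0.29 day at the full mortality margin, given 2 to 15 bed-days lost per extra death, and it favours the intervention when it does harm. The denominator is unstated. If it were admitted patients only, and 6.7 days were their mean, spared 2-day admissions in 5% or 10% of participants would add 0.38 or 0.82 day while total bed-days fall.

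This concerns what one key secondary claim can conclude. The primary analysis and the sample size, which mortality drives, are untouched. The change is worth making before analysis.

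**What to change.** State that the 1-day non-inferiority test is run in every participant of the analysis population, admitted or not, with 0 days for those not admitted. Say which denominator the 6.7-day planning mean uses, and restate that mean if it refers to admitted patients only. Report stay among the admitted as descriptive only.

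Add a supportive analysis of days alive and out of hospital to day 30, with death scored 0 and a bootstrap or robust interval. It should not be a second hurdle, since no margin has been set for it. Read the length-of-stay result beside mortality.

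The cost is some wording and one derived variable. That variable needs discharge, death and 30-day readmission dates. The data collection section describes automatic extraction of outcomes from the electronic record but does not list these dates, and readmissions to other hospitals may be missed.

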### Patient and public involvement

Patient participation is important in both the clinical trial and the implementation of Artificial Intellegence (AI) in clinical practice. The Client Advisory Board of Amsterdam UMC and a former sepsis patient evaluated the study question as relevant and the study design as achievable from patients’ perspective. They will stay involved during the study as well. Also, to disseminate results of the study, we will collaborate with relevant patient organisations. Furthermore, a patient safety and implementation expert was involved in the development of the study protocol and will remain involved during the study period. They will continue to stay involved if the study is deemed successful and the model can be implemented into clinical practice.

## Ethics and dissemination

Obtaining informed consent is of the utmost importance when working with study participants. In order to ensure that participants are well informed about the study before consenting, all potential participants will have the trial clearly explained to them by a trained member of the study team. In addition to the verbal information, a paper information brochure will be provided to each participant, see online supplemental material 1. We inform patients about the procedures and what the consequences of doing or withholding blood cultures can be, as this is the most relevant information for them. Each participant will be made aware of their right to withdraw consent at any given time. If a patient withdraws consent their data will no longer be used in the study and the study personnel will not follow them up. If the patient was in the intervention group and blood culture analysis was already cancelled, we cannot reinstate the analysis, since the material has been destroyed. Due to the nature of the study, the potential participant will get 1 hour to consider joining the study. If any change to the protocol is made the ethics review board will be notified and will have to give permission. If the changes are relevant to the participants, they will receive additional information regarding the changes made.

10.1136/bmjopen-2024-084053.supp1Supplementary data

Research results will be published in peer-reviewed journals approximately 1 year after the trial has ended. This will give the research team sufficient time for statistical analyses.

This study will be conducted according to the principles of the Declaration of Helsinki and in accordance with the Medical Research Involving Human Subjects Act, General Data Privacy Regulation and Medical Device Regulation. The study was approved by the Amsterdam University Medical Center’s medical ethics review committee with number 22.0567. The trial was registered at Clinicaltrials.gov (NCT06163781).

## Discussion

Blood cultures are a commonly used diagnostic tool in the ED. Unfortunately, low yields and high rates of contamination lead to unnecessary use of antibiotics, prolonged length-of-stay in the hospital and even higher mortality. A machine learning model has been validated retrospectively and prospectively and can identify patients at low risk for positive blood cultures. The study described in this protocol is the first randomised controlled trial using machine learning to predict blood culture outcomes. However, possible limits to this trial include restricted future application due to the exclusion of severely immunocompromised patients. Future studies may need to focus on this specific subgroup as well. Nevertheless, this study will include a heterogeneous group presenting to the ED and may greatly influence current standards of practice. By using this model in practice, it can potentially reduce a significant amount of blood culture analyses and prevent the undesirable effects of false-positive blood culture results.
